**Fig 2 pone.0284727.g002:**
[figure not shown]
Study timeline.

**Table 2 pone.0284727.t002:** Exposure variables collected for subsequent prognostic evaluation during the study.

**Patient Factors**	Age at diagnosis, ethnicity, relationship/co-occupancy status, employment status, smoking status, alcohol intake, index of multiple deprivation, medical co-morbidities, current or previous mental health history, family history of mental health conditions and family history of prostate cancer
**Oncological Factors**	Gleason grade and ISUP classification, number of positive biopsy cores, risk stratification, PSA at diagnosis, TNM Score and stage classification.
**Treatment Factors**	Final treatment received, presence of positive surgical margins

Primary study outcomes collected within questionnaires included validated psychometric measures for mental wellbeing post prostate cancer diagnosis. Important mental wellbeing outcomes were defined through multiple extensive and systematic searches of the existing literature due to variable current definitions [7, 9, 10]. This selected five mental wellbeing constructs of interest which will be included within the overall primary outcome of ‘mental wellbeing’:

Depressive SymptomsAnxiety SymptomsFear of Cancer Recurrence/ProgressionBody Image PerceptionMasculine Self-Esteem

Selection of subsequent validated psychometric measures for these outcomes was based on the most utilised tools, or those with the best psychometric properties within a prostate cancer population. These were defined by previous reviews or through a dedicated review for body image and masculinity outcomes [7, 9, 21]. Final psychometric scales selected were:

Patient Health Questionnaire (PHQ)-9—Depression symptoms [22]Generalised Anxiety Disorder (GAD)-7 –Anxiety symptoms [23]Fear of Recurrence Scale 7 (FCR7)—Fear of cancer recurrence/progression [24]Body Image Scale (BIS)–Body image perception [25]Prostate Cancer-Quality of Life (PC-QOL) Masculine Self-Esteem Subset–Masculinity [26]

Importantly, the FCR7 scale items wording was adapted to ensure both recurrence and progression fear was evaluated to ensure ability of both baseline evaluation, and that of individuals not due to undergo curative treatments (e.g., active surveillance or hormone monotherapy). Similarly, the final item of the BIS (dissatisfaction with scar) was removed to ensure consistent evaluation between treatment groups. Internal consistency of these will be evaluated at conclusion through Cronbach’s alpha values to ensure they represent valid measures of these outcomes within the population.

Additional outcomes collected within questionnaires were validated measures of social, physical, and general health including:

The Expanded Prostate Cancer Index Composite-26 (EPIC-26)–Functional/Physical SymptomsFunctional Assessment of Cancer Therapy–General (FACT-G) Social Wellbeing Subscale–Social WellbeingShort Form– 12 (SF12)–Impact of disease on health

These outcomes will be utilised as both dependent and exposure variables depending on the subsequent analysis conducted.

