**Methods:**

MIND-P is a multi-institutional prospective cohort study recruiting newly diagnosed prostate cancer patients for 12-month follow up. It will aim to recruit a final sample of 300 participants undergoing one of four treatment options: active surveillance, radical prostatectomy, radical radiotherapy, or hormone monotherapy. Questionnaire-based data collection consists of multiple validated mental, physical, and social wellbeing outcomes at baseline and 3-monthly intervals until study completion. Primary analysis will include evaluation of treatment undergone against multiple mental wellbeing outcomes. Secondary analysis will additionally explore multiple patient and oncological prognostic factors of potential importance, along with the cumulative incidence of these outcomes, symptom trajectory and their association with subsequent functional and social outcomes.

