## Data collection and outcomes

This questionnaire-based study is conducted remotely, with no physical follow ups within a hospital site. Again, this design was selected to minimise patient risk during the COVID-19 pandemic. Recruited individuals are asked to complete a series of online or postal questionnaires depending on participant preference (S2 File). Participants are requested to complete the same questionnaire containing a battery of validated mental, physical, and social wellbeing measures at baseline, 3-, 6-, 9-, and 12-months (Fig 2). In addition, at baseline participants are requested to complete some demographic information. Reminders are sent to participants at two- and four-weeks post questionnaire dates if not received within this time frame. Participants are then assumed to be no longer interested in participation and marked as lost to follow up if not returned thereafter. Clinical data extraction is also conducted by the research team to collect baseline disease characteristics and subsequent clinical outcomes. A full list of variables to be collected and analysed as exposure/independent variables are included in Table 2. End of study participation will be at 12 months upon completion of the final questionnaire.

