### Primary outcome

Along with the primary objective, the primary study outcome will be the unadjusted mean differences between different management groups of each individual mental wellbeing outcome at 3-, 6-, 9- and 12-months post diagnosis. For this a one-way ANOVA between treatment groups, is planned at each time frame. Subsequent Tukey’s Honest Significant Difference post-hoc analysis will be conducted on any means identified to be statistically significantly different.

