### Sample size

Target sample size calculations are based on the primary aim and outcome of the study evaluating mean differences between different treatment cohorts. This was conducted for hypothesis testing against minimal clinically significant difference (MCSD) of the five mental wellbeing measures of interest, as previously reported in the literature. This was calculated utilising a one-way ANOVA across the four cohorts. Common standard deviation (SD) derived from the literature, or previous pilot data from a small cross-sectional sample were also used to subsequently calculate the effect size f value, with a power of 0.8 and an alpha value of 0.05 utilised. G*Power Software V3.1 [30] was used to calculate the required sample sizes. The largest required sample size across the five mental wellbeing measures was used as the required minimal sample size.

PHQ-9 –MCSD of 5 [31], SD of 3.49 (pilot data)GAD 7 –MCSD of 5 [32], SD of 3.49 (pilot data)FCR7 –MCSD of 10, SD 7.01 [24]BIS–No clear MCSD published in literature [33], use of 10 as cut off for significant symptoms [25], SD of 3.93 (pilot data)Masculine Self-Esteem MCSD of 9.8 [34], SD of 15.79 [35]

Sample size calculations utilising the above values revealed a maximum requirement of 232 participants (58 per cohort) using the PC-QOL Masculine Self-Esteem Scale. Assuming a reasonable dropout rate of 25%, a requirement of 75 participants per cohort was set to give an overall target sample of 300 participants. During recruitment, individual treatment cohorts of these sizes will be targeted, with a gradual stop in recruitment across these different cohorts to gain sizes of groups as close to equal as possible. However, due to likely unequal dropout rates and some crossover to different treatment arms during follow up (e.g. those undergoing surveillance subsequently undergoing radical treatment) it is likely some disparity in cohort sizes will exist. These would subsequently require consideration within analysis and conclusions drawn from study results if any individual cohort contains fewer than the minimum sample size described above.

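### The grouping rule for the primary comparison is inconsistent and points to final treatment, so scores from before a switch can be counted under a treatment not yet received

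*Protocol article*

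**What the plan says.** Several places in the protocol article bear on which group a man belongs to, and they do not agree.

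Pointing to final treatment:
- Data collection and outcomes: "A full list of variables to be collected and analysed as exposure/independent variables are included in Table 2". The treatment row of that table reads "Final treatment received, presence of positive surgical margins". No other variable there identifies the treatment group.
- Abstract, Methods: "Primary analysis will include evaluation of treatment undergone against multiple mental wellbeing outcomes".
- Sample size: besides unequal dropout, the section cites "some crossover to different treatment arms during follow up (e.g. those undergoing surveillance subsequently undergoing radical treatment) it is likely some disparity in cohort sizes".

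Pointing to planned or baseline management:
- Population: a man must be due to undergo one of the four options and must not already have had it. Cohorts are therefore formed on planned management.
- Secondary outcomes: the treatment factors entering the prognostic model are described as baseline factors.

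Neutral:
- Primary outcome: "the primary study outcome will be the unadjusted mean differences between different management groups of each individual mental wellbeing outcome", at 3, 6, 9 and 12 months. "For this a one-way ANOVA between treatment groups, is planned at each time frame". Neither sentence names the grouping variable.

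The only stated response to crossover is in Sample size: "These would subsequently require consideration within analysis and conclusions drawn from study results if any individual cohort contains fewer than the minimum sample size".

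**The concern.** A one-way ANOVA at 3 months needs groups that are known by 3 months. Grouping by final treatment breaks this. A man on surveillance until month 9 who then has surgery would have his 3- and 6-month scores, all recorded on surveillance, averaged into the prostatectomy cohort. The surveillance cohort would be reduced to men who stayed on it. If the decision to leave is related to how a man feels, membership is related to the outcome through an event after baseline.

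The secondary prognostic model has the same fault. It relates treatment factors to symptoms that develop during follow-up, and those symptoms may precede the treatment said to predict them. Surgical margins, in the same row of Table 2, are likewise not known at baseline.

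At stake is the contrast between surveillance and radical treatment, which is part of the comparison the study is powered for. The planned response concerns cohort size only. It does not address misclassified visits.

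**Working it through.** **1. The plan's own figure.** Masculine self-esteem sets the sample size: difference 9.8, SD 15.79, so d = 9.8/15.79 = 0.62 SD. With two extreme means and two at the midpoint, f = d × √(1/8) = 0.2194. A four-group ANOVA at alpha 0.05 and power 0.80 then needs 232 men (power 0.803), as the protocol states. This assumes fixed cohorts and gives 0.62 SD as the yardstick.

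**2. Shift caused by grouping on final treatment, at a visit before the switch.** The documents give no crossover rate and no scores for switchers, so all inputs except the cohort size of 75 are assumptions. Scores are coded so that higher is worse.
- p: share of surveillance men who later switch, all into one radical cohort
- s: switchers' mean minus stayers' mean before the switch, in SD
- R: radical minus surveillance difference by planned management, in SD

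Set the mean of all men enrolled for surveillance to 0. Stayers then average −ps and switchers (1 − p)s. The receiving cohort, 75 men plus 75p switchers, averages [R + p(1 − p)s]/(1 + p).

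Contrast by final treatment minus contrast by planned management:

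[R + p(1 − p)s]/(1 + p) + ps − R = p(2s − R)/(1 + p)

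A positive value favours surveillance.

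| R | s | p = 15% | p = 20% | p = 30% |
|---|---|---|---|---|
| 0 | +0.5 | +0.13 | +0.17 | +0.23 |
| 0 | 0 | 0 | 0 | 0 |
| 0 | −0.5 | −0.13 | −0.17 | −0.23 |
| 0.62 | +0.5 | +0.05 | +0.06 | +0.09 |
| 0.62 | 0 | −0.08 | −0.10 | −0.14 |

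Example: p = 0.15, s = 0.5, R = 0 gives 0.15 × 1.0/1.15 = 0.130. With R = 0, s from 0.3 to 0.8 and p from 10% to 30%, the range is 2 × 0.1 × 0.3/1.1 = 0.055 to 2 × 0.3 × 0.8/1.3 = 0.369.

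The shift favours surveillance only if s exceeds R/2. Otherwise it is nil or runs the other way, because men not yet treated dilute the radical cohort.

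**3. False-positive rate.** This was simulated with 3,000 runs per setting, 58 per cohort, equal means by planned management, and switchers divided between two radical cohorts and scoring 0.3–1.0 SD worse than stayers. The table gives rejection rates for one ANOVA at a pre-switch visit.

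| Crossover | Final treatment | Planned management |
|---|---|---|
| 10% | 0.05–0.11 | about 0.04 |
| 20% | 0.07–0.23 | 0.04–0.05 |
| 30% | 0.07–0.38 | 0.04–0.06 |

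Reversing the sign of every score leaves the F statistic unchanged, so switchers who score better by the same amount inflate the rate equally.

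**4. Cohort size.** If switchers leave their cohort, 20% crossover takes surveillance from 75 to 60, and 25% dropout takes it to 45. The stated minimum is 58. Without crossover the figure is 75 × 0.75 = 56.25.

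**The case against.** The strongest reply is that nothing in the document says the primary ANOVA groups by final treatment. Table 2 is titled as a list for prognostic evaluation, which is a secondary aim. Its treatment variable may simply mean the treatment a man went on to have, as distinct from what the multi-disciplinary team suggested. This stands against the reading that the protocol defines its cohorts by final treatment; it does not say so. It does not remove the inconsistency. The text calls Table 2 the full list of exposure variables, the abstract analyses treatment undergone, and crossover can alter cohort sizes only if switchers leave the cohort they entered.

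A reader might also infer that the bias runs towards the study hypothesis of surveillance best and hormone monotherapy worst. The documents do not support that. They say nothing about switchers' scores, and the sign depends on them. The Study aims expect body image and masculinity symptoms to rise with treatment side effects, so adding untreated men to a surgical cohort could hide a difference. If switchers do score worse, they worsen a radical cohort and narrow its gap to hormone monotherapy, against the hypothesis.

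The misclassification should be least at 12 months, when most switches lie in the past. The study is also framed as exploratory and non-causal. That limits the claims made from it, but a prognostic factor still has to be known before the outcome it is meant to predict.

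Grouping by planned management has its own limit: men enrol before surgery or radiotherapy, so some early scores will still precede treatment. But membership no longer depends on later events.

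Finally, a reader might infer that the absence of a separate variable for combined hormone therapy is part of the same fault. How the treatment variable is coded is detail that an article may leave to the full protocol, and it does not carry this point.

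**Conclusion.** The concern holds as an inconsistency with a consequence. The protocol does not fix which management defines the groups, most of its wording points to final treatment, and under that reading the 3-, 6- and 9-month comparisons and the secondary prognostic model can count scores or symptoms from before a switch under a later treatment.

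The effect can go either way. The figure of 0.13–0.23 SD in favour of surveillance, against a design difference of 0.62 SD, rests on four assumptions: 15–30% crossover, all into one radical cohort; switchers 0.5 SD worse before switching; no switch before the visit analysed; and equal means by planned management. It falls to 0.05–0.09 SD if the true contrast equals the design difference, and is nil or reversed if switchers score the same or better. No directional bias towards the hypothesis is established. Leaving the rule open is itself a weakness, because the choice can change the result and could be made after the data are seen.

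**What to change.** State in Primary outcome that the four cohorts are defined by the management each man was due to undergo at enrolment, and that he stays in that cohort at every visit. Use this eligibility criterion, not the team's suggested strategy, because a man may have chosen another option before enrolling. Apply the same grouping in the secondary prognostic model, and amend Table 2 and the crossover sentence in Sample size to agree.

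Add a sensitivity analysis that classifies each man by the treatment actually received by each questionnaire date. Report final treatment, and the number and timing of switches, descriptively.

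The cost is wording, plus treatment dates from the clinical data extraction already planned. The downside is that crossover slightly dilutes the contrast between cohorts; the sensitivity analysis shows by how much. The rule should be fixed before any outcome is compared between groups.

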### Statistical analysis

Descriptive statistics will be calculated for the study population and individual study outcomes. Important definitions to be utilised throughout the data analysis are the threshold set for significant mental wellbeing symptoms in each of the measures collected. For depressive or anxiety symptoms a score of 10 or greater on the PHQ-9 or GAD 7 scales will be used for depression and anxiety respectively, representing moderate symptoms and has been demonstrated to correlate well to depressive or anxiety disorders diagnoses [23, 27]. For the FCR7 scale, a value of 17 or greater was selected, being representative of moderate fear of recurrence/progression as per the tool’s original development [24]. For the BIS, a cut of 10 or greater was selected as a previously demonstrated useful clinically relevant cut off point [28]. Finally, no clear-cut offs exist for the PC-QOL masculine self-esteem subset specifically. However, previously the tool authors have utilised scores of less than 60 to signify a low score for other subsets of the scale, and hence this was selected for this study [29].

Missing data during study follow-up through participant loss to follow up is expected, impacting subsequent analyses for primary and secondary outcomes. Where possible, multiple imputation will be considered for missing outcome data, with complete case analysis to be used for analyses where this is not possible.

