### Secondary outcomes

The following outcomes are not accounted for within the sample size calculations and are therefore considered exploratory. Each planned analysis will be divided per secondary aim of the study.

For exploration of prognostic factors of mental wellbeing outcomes, baseline patient, oncological and treatment factors previously described will be evaluated against the binary outcome of the development of significant individual mental wellbeing symptoms during study follow up. For this analysis an initial univariable, followed by a multivariable regression analysis of potentially significant individual prognostic factors is planned.The cumulative incidence of developing significant individual mental wellbeing outcomes during the 12-month study follow up will be calculated and presented as a percentage.To evaluate the trajectory of mental wellbeing symptoms over a 12-month period and effect of time on symptom scores, mental wellbeing outcome scores of whole cohort and individual treatment cohorts will be evaluated at each follow up time. Evaluation of these scores will be conducted using multilevel mixed-effects analyses to account for the effect of recruitment site clustering and expected loss to follow up during the study.The relationship between each individual mental wellbeing symptom and functional, social, and general health outcomes will be evaluated. Functional outcomes will include sexual, urinary and bowel symptoms from EPIC-26. Social wellbeing will include FACT-G subscale scores with general health defined using the SF-12 physical component score. All outcomes will be evaluated at 12-months. For this each mental wellbeing symptom will be continuously evaluated against these outcomes using univariable and subsequent multivariable linear regression, adjusted for known factors for functional and social outcomes.

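### The Body Image Scale cut-off of 10 is carried over to a shortened scale without rescaling or justification, and may under-count cases in two exploratory analyses, chiefly after prostatectomy

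*Protocol article*

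**What the plan says.** In Data collection and outcomes, the protocol article adapts two instruments. For the Body Image Scale (BIS), "the final item of the BIS (dissatisfaction with scar) was removed to ensure consistent evaluation between treatment groups". The only check announced for the adapted scales is this: "Internal consistency of these will be evaluated at conclusion through Cronbach’s alpha values".

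The Statistical analysis section then fixes the thresholds for significant symptoms. "For the BIS, a cut of 10 or greater was selected as a previously demonstrated useful clinically relevant cut off point", citing reference [28]. The Sample size section uses the same value, "use of 10 as cut off for significant symptoms [25], SD of 3.93 (pilot data"; reference [25] is the one the article gives for the BIS itself. Neither section mentions the removed item, a prorated score or an adjusted threshold.

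Under Secondary outcomes the threshold enters two analyses: the prognostic regressions, whose outcome is "the binary outcome of the development of significant individual mental wellbeing symptoms during study follow up", and "The cumulative incidence of developing significant individual mental wellbeing outcomes during the 12-month study follow up". That section labels these analyses exploratory. The primary analysis does not use the threshold: "the primary study outcome will be the unadjusted mean differences between different management groups of each individual mental wellbeing outcome".

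**The concern.** A cut-off on a summed score is tied to the items that make up the sum. The item was dropped for this study's own purpose, and the cut-off is presented as coming from earlier work, so the natural reading is that 10 was established with the item in place. Applied to fewer items, the same number cannot be easier to reach and may be harder.

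At stake are the percentage reported as 12-month incidence of significant body image symptoms and the case definition in the body image regressions. The Discussion hopes the study will highlight how common these problems are and identify men at higher risk. A percentage at 10 or more on the shortened scale is not on the same footing as one from studies that scored the full scale. Any shortfall would also fall unevenly across treatment groups, and treatment is one of the factors to be examined.

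**Working it through.** **Inputs from the protocol article.** Scar item removed (Data collection and outcomes); cut-off 10 or greater (Statistical analysis); pilot SD 3.93 for the BIS, masculine self-esteem difference 9.8 with SD 15.79, four groups, alpha 0.05, power 0.80, maximum N 232 (Sample size). The article does not give the number of items, their range, the scoring rule, the BIS mean, or whether the pilot SD came from the full or the shortened scale.

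**1. The plan's own figure, and whether the cut-off touches it.** With two extreme means and the other two midway, f = (difference/SD)/√(2 × 4).
- Masculine self-esteem: (9.8/15.79)/√8 = 0.219. The noncentral F distribution gives 58 per group, N = 232, matching the protocol.
- BIS with 10: (10/3.93)/√8 = 0.900, N = 20. BIS with 9: (9/3.93)/√8 = 0.810, N = 24.

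The maximum stays at 232, so the sample size is unaffected.

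**2. Direction.** Let S be the shortened total and x ≥ 0 the scar item, so the full total is S + x. If S ≥ 10 then S + x ≥ 10. The share at 10 or more on the shortened scale therefore never exceeds that on the full scale. A man is lost only if S < 10 and S + x ≥ 10. If x = 0, nothing changes for him.

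**3. What prorating does to the cut.** With k original items, a prorated score of 10 needs S ≥ 10(k − 1)/k. For k = 8, 9, 10, 11, 12 this is 8.75, 8.89, 9.00, 9.09, 9.17. With whole-number totals and complete answers, that means 9 or more for k = 8 to 10, but still 10 or more for k = 11 or 12. Prorating reclassifies men only if the original scale has ten items or fewer.

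**4. Illustrative size.** Assumed: ten summed items scored 0 to 3, one common latent factor, and a removed item that behaves like the others; 400,000 simulated men per scenario. For the surgical-quarter column, full-scale rate = 0.25 × (ten-item rate) + 0.75 × (nine-item rate), taking 75 of 300 men as surgical and the rest as scoring 0 on the scar item.

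| Nine-item mean | Loading | Nine-item SD | Ten items ≥10 | Nine items ≥10 | Nine items ≥9 (prorated ≥10) | Cases lost if all can score | Cases lost if a surgical quarter can |
|---|---|---|---|---|---|---|---|
| 3 | 0.60 | 3.29 | 7.18% | 5.40% | 7.45% | 25% | 8% |
| 3 | 0.75 | 3.99 | 10.12% | 8.25% | 10.33% | 18% | 5% |
| 5 | 0.60 | 4.31 | 19.06% | 15.33% | 19.50% | 20% | 6% |
| 5 | 0.75 | 5.17 | 21.56% | 18.27% | 21.83% | 15% | 4% |
| 7 | 0.60 | 5.01 | 33.53% | 28.26% | 33.91% | 16% | 4% |
| 7 | 0.75 | 5.99 | 34.50% | 30.23% | 34.77% | 12% | 3% |

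The second row is closest to the pilot SD of 3.93. There, 1 − 8.25/10.12 = 18% of cases are lost if all men can score. If only a surgical quarter can, the full-scale rate is 0.25 × 10.12 + 0.75 × 8.25 = 8.72%, and 1 − 8.25/8.72 = 5% are lost.

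**5. Prorating can err the other way.** In that same row, if only the surgical quarter can score, the prorated definition counts 10.33% against 8.72%, an excess of 1.61 percentage points.

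**6. The planned check.** Cronbach's alpha is computed from item variances and covariances. No cut-off or external criterion enters it, so it cannot show whether 10 still marks the same severity.

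**The case against.** The strongest reply is that for most of the sample nothing may change. Three of the four cohorts have no surgical scar from their treatment. Men already operated on are excluded at entry, so the prostatectomy cohort has no such scar at baseline either. For a man who would score 0 on the item, 10 on the shortened scale is exactly 10 on the full scale. This stands, and it limits the point to a possible under-count.

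A reader might infer that cases are certainly under-counted throughout the cohort, by a fifth to a quarter. The documents do not support that. Moving the cut from 10 to 9 on an assumed gamma distribution with SD 3.93 and a mean of 3 to 6 does give a relative loss of 20–24%. But that compares two cuts on one curve and treats the scar item as an average item in every man.

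The item was also removed deliberately so that all groups answer the same questions. That is a sound reason for the shortened score, but it does not justify keeping the threshold.

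Finally, the cited sources are not at hand, so it cannot be confirmed that 10 was established on the full scale, and an article may leave scoring detail to the full protocol. Both are fair cautions. However, the article itself fixes the threshold and describes the item removal, and does not connect the two.

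**Conclusion.** The point holds in a limited form. A cut-off most naturally read as a full-scale one is applied to a shortened scale without rescaling or justification, and the planned internal-consistency check cannot test it. If items are non-negative and summed, any resulting error in caseness relative to the full scale is towards under-counting, and it falls chiefly on men after prostatectomy.

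The size cannot be derived from the documents. Under the assumed ten-item structure, the loss is about 5% of cases in the scenario nearest the pilot SD if only a surgical quarter can score on the item (3–8% over all scenarios), and 12–25% if every man can.

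The reach is confined to the exploratory cumulative incidence and binary prognostic-factor analyses for body image. A reader might take the point to undermine the main treatment comparison or the target of 300. It does not, because the primary ANOVA compares mean scores and masculine self-esteem sets the sample size.

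**What to change.** - State in Statistical analysis that the BIS cut-off is carried over to a version without the scar item, give the scoring rule and the original number of items, and reconcile the two references cited for the value of 10.
- Keep 10 or greater as the stated definition.
- Add a sensitivity analysis that repeats the body image incidence and prognostic regressions on the prorated score (mean item score × original number of items, 10 or greater), reported by treatment group.
- Do not compare the unadjusted percentage directly with studies that used the full scale.

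The cost is a few lines of wording and one repeated analysis, with no new data. The small downside is that prorating assumes the removed item behaves like the others, so it may over-count men without a surgical scar. The two results should be read as a range. Its upper end is not a strict bound, since men with a scar could score above their average on that item. If the original scale has more than ten items, the two definitions coincide for complete questionnaires, and the report should say so.
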